**A21. How long do you expect each participant to be in the study in total?**

PART A: Seven laboratory visits (20-90 mins per visit) over a one-month period.

PART B: Seven laboratory visits (20-90 mins per visit) over a one-month period.

**A22. What are the potential risks and burdens for research participants and how will you minimise them?**

*For all studies, describe any potential adverse effects, pain, discomfort, distress, intrusion, inconvenience or changes to lifestyle. Only describe risks or burdens that could occur as a result of participation in the research. Say what steps would be taken to minimise risks and burdens as far as possible.*

The collection of blood samples may cause discomfort, minor bruising, and carries a risk of infection - blood samples will be collected by a trained phlebotomist wearing the correct personal protective equipment (e.g. disposable gloves, laboratory coat). All surfaces (e.g. chair, tables) will be cleaned before and after use and the researcher will practice hand washing prior to touching any equipment.

Performing the resistance exercise may cause musculoskeletal injury - A readiness to exercise questionnaire will be

completed prior to testing and participants will not be eligible to participate if they have a current or previous (past 3 months) musculoskeletal injury. Participants will be demonstrated correct lifting technique; perform an appropriate warm-up; and be supervised at all times.

Performing the Pressure-Pain Threshold test with a pressure algometer may cause discomfort and minor bruising - The participant will be instructed to indicate when the pressure applied with the algometer becomes painful, at which point, the pressure will be released. The test will be performed on alternate legs to reduce bruising of the same site and participants will be advised to treat any bruising with rest, ice, compression, and elevation.

Assessing body composition by dual energy X-ray absorptiometry exposes the participant to a small amount of ionising radiation. The effective dose has been reviewed and approved by the Medical Physics Expert and the Clinical Radiation Expert. Immediately prior to each DXA scan, female participants will be required to sign confirmation that they are not pregnant nor do they suspect that they may be pregnant.

There is a risk of spreading or being infected with Covid-19. The laboratory has a maximum occupancy that will be adhered to; a 2 metre distance will be maintained where possible; where close contact is required e.g. when taking blood samples, performing the pressure-pain threshold test, and measuring leg circumference, a face covering will be worn by both the researcher and participant and the researcher will wear disposable gloves; all surfaces including the exercise equipment will be cleaned before and after use with the correct cleaning solution; frequent hand-washing will be performed; and if either a participant or the researcher develops Covid-19 symptoms they will be instructed not to attend the laboratory and to self-isolate in line with government guidance.

#### **A24. What is the potential for benefit to research participants?**

Participants will receive a full body composition analysis from their DXA scans and a dietary analysis performed by a registered sport nutritionist. Participants will be informed of their maximum leg strength (1RM) which can be useful for exercise training programmes. Participants will also learn how to complete resistance exercises which can be of benefit to their musculoskeletal health.

### **RECRUITMENT AND INFORMED CONSENT**

*In this section we ask you to describe the recruitment procedures for the study. Please give separate details for different study groups where appropriate.*

#### **A27-1. How will potential participants, records or samples be identified? Who will carry this out and what resources will be used?** *For example, identification may involve a disease register, computerised search of GP records, or review of medical records. Indicate whether this will be done by the direct healthcare team or by researchers acting under arrangements with the responsible care organisation(s).*

Participants will be identified from the Durham University staff and student base, as well as external to the University but locally to the region. Participants will be recruited by the primary researcher and supervisors. A recruitment email detailing the research project and eligibility criteria, including a participant information sheet, will be circulated around the university staff and student mailing list and via the weekly 'dialogue' newsletter. Posters detailing the study will be displayed in communal areas around the university, with contact details of the primary researcher. Social media (Twitter, LinkedIn) will be used to advertise the study, alongside details of how to get more information and to contact the primary researcher.

#### **A27-2. Will the identification of potential participants involve reviewing or screening the identifiable personal information of patients, service users or any other person?**

☐ Yes ☒ No

*Please give details below:*

#### **A28. Will any participants be recruited by publicity through posters, leaflets, adverts or websites?**

☒ Yes ☐ No

*If Yes, please give details of how and where publicity will be conducted, and enclose copy of all advertising material (with version numbers and dates).*

Posters will be placed in communal areas of Durham University buildings. An electronic version of the poster will be distributed via social media platforms (Twitter, LinkedIn). These will detail the study and provide contact details of the lead researcher.

**A29. How and by whom will potential participants first be approached?**

The participants will be recruited by the primary researcher and supervisors. A recruitment email detailing the research project and eligibility criteria, including a participant information sheet, will be circulated around the university staff and student mailing list. Interested participants will be asked to contact the lead researcher for further detail.

**A30-1. Will you obtain informed consent from or on behalf of research participants?**

☒ Yes ☐ No

*If you will be obtaining consent from adult participants, please give details of who will take consent and how it will be done, with details of any steps to provide information (a written information sheet, videos, or interactive material). Arrangements for adults unable to consent for themselves should be described separately in Part B Section 6, and for children in Part B Section 7.*

*If you plan to seek informed consent from vulnerable groups, say how you will ensure that consent is voluntary and fully informed.*

Participants will be provided a participant information sheet and privacy notice, alongside the informed consent form. They will be given the opportunity to ask any questions prior to signing the informed consent form, which will be received by the lead researcher.

*If you are not obtaining consent, please explain why not.*

*Please enclose a copy of the information sheet(s) and consent form(s).*

**A30-2. Will you record informed consent (or advice from consultees) in writing?**

☒ Yes ☐ No

**A31. How long will you allow potential participants to decide whether or not to take part?**

Participants will have as long as they wish to decide whether or not to participate, up until the study has terminated. The minimum time for consideration will be 7 days.

**A32. Will you recruit any participants who are involved in current research or have recently been involved in any research prior to recruitment?**

☒ Yes  
☐ No  
☐ Not Known

*If Yes, please give details and justify their inclusion. If Not Known, what steps will you take to find out?*

Participants who are currently taking part in another research project will not be included. Participants who have previously been involved in research may be included, but not if the research involved dietary and/or exercise intervention and was conducted in the past 6 months.

**A33-1. What arrangements have been made for persons who might not adequately understand verbal explanations or written information given in English, or who have special communication needs?(e.g. translation, use of interpreters)**

There are not the funds to support a translator and therefore individuals who are unable to understand the written or verbal information, will not be permitted to take part in the study.

**A35. What steps would you take if a participant, who has given informed consent, loses capacity to consent during the study? Tick one option only.**

- ☒ The participant and all identifiable data or tissue collected would be withdrawn from the study. Data or tissue which is not identifiable to the research team may be retained.
- ☐ The participant would be withdrawn from the study. Identifiable data or tissue already collected with consent would be retained and used in the study. No further data or tissue would be collected or any other research procedures carried out on or in relation to the participant.
- ☐ The participant would continue to be included in the study.
- ☐ Not applicable – informed consent will not be sought from any participants in this research.
- ☐ Not applicable – it is not practicable for the research team to monitor capacity and continued capacity will be assumed.

*Further details:*

## CONFIDENTIALITY

In this section, personal data means any data relating to a participant who could potentially be identified. It includes pseudonymised data capable of being linked to a participant through a unique code number.

### Storage and use of personal data during the study

**A36. Will you be undertaking any of the following activities at any stage (including in the identification of potential participants)? (Tick as appropriate)**

- ☐ Access to medical records by those outside the direct healthcare team
- ☐ Access to social care records by those outside the direct social care team
- ☒ Electronic transfer by magnetic or optical media, email or computer networks
- ☐ Sharing of personal data with other organisations
- ☐ Export of personal data outside the EEA
- ☒ Use of personal addresses, postcodes, faxes, emails or telephone numbers
- ☐ Publication of direct quotations from respondents
- ☐ Publication of data that might allow identification of individuals
- ☐ Use of audio/visual recording devices
- ☒ Storage of personal data on any of the following:
- ☒ Manual files (includes paper or film)
  - ☐ NHS computers
  - ☐ Social Care Service computers
  - ☐ Home or other personal computers
  - ☒ University computers
  - ☐ Private company computers
  - ☒ Laptop computers

*Further details:*

Personal information will only be used to contact the participant. All information will be stored on password protected devices and an encrypted memory stick.

**A38. How will you ensure the confidentiality of personal data?** Please provide a general statement of the policy and procedures for ensuring confidentiality, e.g. anonymisation or pseudonymisation of data.

All data files will be stored on computers or laptops with passwords that are only known by the research team and any hard copies will be stored in a locked filing cabinet which only the researchers can access. Participants' names will not be used to label data files and samples collected. Instead, each will be given an anonymous participant code, which will only be known by the research team. This way none of the other participants or anyone outside of the research team will be able to identify which test data belongs to which participant. The data presented in the written manuscript will not be identifiable to specific participants. After six months, all data will be anonymised and identifiable original data will be destroyed.

**A40. Who will have access to participants' personal data during the study?** Where access is by individuals outside the direct care team, please justify and say whether consent will be sought.

Only the lead researcher ([name]) and supervisors ([name] and [name]) will have access to participants' personal data.

#### Storage and use of data after the end of the study

**A43. How long will personal data be stored or accessed after the study has ended?**

- ☐ Less than 3 months  
☒ 3 – 6 months  
☐ 6 – 12 months  
☐ 12 months – 3 years  
☐ Over 3 years

#### INCENTIVES AND PAYMENTS

**A46. Will research participants receive any payments, reimbursement of expenses or any other benefits or incentives for taking part in this research?**

- ☐ Yes ☒ No

**A47. Will individual researchers receive any personal payment over and above normal salary, or any other benefits or incentives, for taking part in this research?**

- ☐ Yes ☒ No

**A48. Does the Chief Investigator or any other investigator/collaborator have any direct personal involvement (e.g. financial, share holding, personal relationship etc.) in the organisations sponsoring or funding the research that may give rise to a possible conflict of interest?**

- ☐ Yes ☒ No

#### NOTIFICATION OF OTHER PROFESSIONALS

**A49-1. Will you inform the participants' General Practitioners (and/or any other health or care professional responsible for their care) that they are taking part in the study?**

☐ Yes ☒ No

*If Yes, please enclose a copy of the information sheet/letter for the GP/health professional with a version number and date.*

## PUBLICATION AND DISSEMINATION

### A50. Will the research be registered on a public database?

*The UK Policy Framework for Health and Social Care Research sets out the principle of making information about research publicly available. Furthermore: Article 19 of the World Medical Association Declaration of Helsinki adopted in 2008 states that "every clinical trial must be registered on a publicly accessible database before recruitment of the first subject"; and the International Committee of Medical Journal Editors (ICMJE) will consider a clinical trial for publication only if it has been registered in an appropriate registry. Please see guidance for more information.*

☒ Yes ☐ No

*Please give details, or justify if not registering the research.*

The study will be registered on a clinical trials registry following ethical approval - <https://www.isrctn.com/>

*Please ensure that you have entered registry reference number(s) in question A5-1.*

### A51. How do you intend to report and disseminate the results of the study? Tick as appropriate:

- ☒ Peer reviewed scientific journals
- ☐ Internal report
- ☒ Conference presentation
- ☐ Publication on website
- ☐ Other publication
- ☐ Submission to regulatory authorities
- ☐ Access to raw data and right to publish freely by all investigators in study or by Independent Steering Committee on behalf of all investigators
- ☐ No plans to report or disseminate the results
- ☒ Other (please specify)

PhD Thesis

### A53. How and when will you inform participants of the study results?

*If there will be no arrangements in place to inform participants please justify this.*

Participants will be offered a lay summary via email, once the results have been published in a peer review journal.

## 5. Scientific and Statistical Review

### A54. How has the scientific quality of the research been assessed? Tick as appropriate:

- ☐ Independent external review
- ☐ Review within a company
- ☐ Review within a multi-centre research group
- ☐ Review within the Chief Investigator's institution or host organisation
- ☒ Review within the research team
- ☒ Review by educational supervisor
- ☐ Other

*Justify and describe the review process and outcome. If the review has been undertaken but not seen by the researcher, give details of the body which has undertaken the review:*

The study proposal has been reviewed by [name] and [name]. This review included concept and supporting literature, objectives, study design, inclusion/exclusion criteria, recruitment of participants, primary and secondary outcome measures, methodology and the statistical analysis plan. In addition, the proposal has been reviewed by a panel of independent academics at Durham University, as part of the annual doctorate review. The review process has taken approximately 3 months and the proposal was approved by the supervisory team.

*For all studies except non-doctoral student research, please enclose a copy of any available scientific critique reports, together with any related correspondence.*

*For non-doctoral student research, please enclose a copy of the assessment from your educational supervisor/ institution.*

**A56. How have the statistical aspects of the research been reviewed? Tick as appropriate:**

- ☐ Review by independent statistician commissioned by funder or sponsor
- ☐ Other review by independent statistician
- ☐ Review by company statistician
- ☐ Review by a statistician within the Chief Investigator's institution
- ☐ Review by a statistician within the research team or multi-centre group
- ☒ Review by educational supervisor
- ☐ Other review by individual with relevant statistical expertise
- ☐ No review necessary as only frequencies and associations will be assessed – details of statistical input not required

*In all cases please give details below of the individual responsible for reviewing the statistical aspects. If advice has been provided in confidence, give details of the department and institution concerned.*

|              |                                 |
|--------------|---------------------------------|
|              | Title Forename/Initials Surname |
|              | [name]                   |
| Department   | Sport and Exercise Sciences     |
| Institution  | Durham University               |
| Work Address | [name]                    |
|              | Durham                          |
| Post Code    | [name]                         |
| Telephone    |                                 |
| Fax          |                                 |
| Mobile       |                                 |
| E-mail       | [contact]         |

*Please enclose a copy of any available comments or reports from a statistician.*

**A57. What is the primary outcome measure for the study?**

Exercise-induced changes in markers of muscle damage

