**2. OVERVIEW OF THE RESEARCH**

*To provide all the information required by review bodies and research information systems, we ask a number of specific questions. This section invites you to give an overview using language comprehensible to lay reviewers and members of the public. Please read the guidance notes for advice on this section.*

**A6-1. Summary of the study.** *Please provide a brief summary of the research (maximum 300 words) using language easily understood by lay reviewers and members of the public. Where the research is reviewed by a REC within the UK Health Departments' Research Ethics Service, this summary will be published on the Health Research Authority (HRA) website following the ethical review. Please refer to the question specific guidance for this question.*

Unaccustomed resistance exercise can cause damage to muscle fibres that may consequently lead to muscle soreness, loss of strength, and reduced flexibility for several days following the exercise bout. These impairments prolong recovery time and likely impact exercise performance, which over time, may limit the gains in muscle mass and strength associated with resistance training. Therefore, establishing strategies to limit exercise-induced muscle damage will be advantageous to exercising individuals. This research will investigate the impact of exercise intensity in both sexes (part A) and dietary protein feeding (part B) as potential strategies for reducing muscle damage.

For part A of the research, young, healthy males and females (n = 40) will be recruited. Participants will perform a single bout of leg-based resistance exercise using either heavy or lighter weights. Muscle damage will be assessed before, immediately after, and in 24-hour intervals after the exercise through indirect blood markers (from blood samples), self-perceived muscle soreness (via pressure algometry), and muscle function (strength and flexibility). Muscle damage will be compared between sexes and exercise loads, and related to total lean body mass, as determined by dual energy X-ray absorptiometry (DXA) at baseline.

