Immediately following the exercise bout (post), another venous blood sample will be taken (3 x 8.5-10 mL) and the measures of limb circumference, range of motion, and muscle soreness will be repeated. Then, participants will be provided a dairy yoghurt containing 20 g of milk protein to stimulate muscle repair and growth. These four measures (excluding protein consumption) will be repeated during the morning of visits four (+24 h), five (+48 h), six (+72 h), and seven (+168 h). Also, during visits six and seven, the 1RM strength test will be repeated on the leg press and leg extension. Over the experimental period, a total of 171 mL of blood will be collected from each participant. This is the equivalent of ~34 teaspoons and is a common amount obtained during exercise physiology research. The blood samples will be used to analyse serum concentrations of creatine kinase, myoglobin (markers of muscle damage), C-reactive protein, and interleukin-6 (markers of inflammation).

**OBJECTIVE 2/PART B:** This study will employ a randomised parallel groups design, for which 22 healthy females aged 18-35 years will be recruited. Prior to the first laboratory visit, prospective participants will have the opportunity to ask questions and gain further information about the study via a video/phone call with the lead researcher. If willing to participate, participants will be asked to electronically sign a consent form. Participants will be asked to record their menstrual cycle and inform the lead researcher at the onset of menses – this information will be used to arrange the time of the baseline assessments, as all measures will be conducted during the late follicular phase of the menstrual cycle.

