**A58. What are the secondary outcome measures?(if any)**

Precision assessment of dual energy X-ray absorptiometry

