**A59. What is the sample size for the research? How many participants/samples/data records do you plan to study in**

*total? If there is more than one group, please give further details below.*

Total UK sample size: 62

Total international sample size (including UK):

Total in European Economic Area:

*Further details:*

PART A: 20 males and 20 females

PART B: 22 females

**A60. How was the sample size decided upon?** *If a formal sample size calculation was used, indicate how this was done, giving sufficient information to justify and reproduce the calculation.*

PART A: A statistical power analysis was conducted. It was determined that a sample size of 8 per group was required to have 80% power to detect a between-group difference in muscle strength of 14%, when using a dependent t-test with a 0.05 two-sided significance level. A ~20% drop-out is anticipated, therefore, 10 males and 10 females in both groups will be recruited (n = 40 total).

PART B: A statistical power analysis was conducted. It was determined that a sample size of 9 per group was required to have 80% power to detect a between-group difference in muscle strength of 13%, when using a dependent t-test with a 0.05 two-sided significance level. A ~20% drop-out is anticipated, therefore, a total of 22 females will be recruited.

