**A61. Will participants be allocated to groups at random?**

☒ Yes ☐ No

*If yes, please give details of the intended method of randomisation:*

With each eligible participant identified, a coin will be tossed to decide which group they go into.

**A62. Please describe the methods of analysis (statistical or other appropriate methods, e.g. for qualitative research) by which the data will be evaluated to meet the study objectives.**

PART A: The Shapiro Wilk test will be used to assess the distribution of the data and to ensure no assumptions for statistical models are violated. Any data that violate the assumptions will be logarithmically transformed before statistical analysis. A two-way mixed design analysis of variance (ANOVA) will be used to analyse each muscle damage marker between exercise conditions and within time points. A two-way between-subjects ANOVA will be used to analyse each muscle damage marker between exercise conditions and between sexes. Independent t tests with Bonferroni corrections will be used to compare time-points between exercise conditions for all measures. Paired t tests will be used to detect any significant within-group changes between time points.

PART B: The Shapiro Wilk test will be used to assess the distribution of the data and to ensure no assumptions for statistical models are violated. Any data that violate the assumptions will be logarithmically transformed before statistical analysis. A two-way mixed design ANOVA will be used to analyse each muscle damage marker between dietary conditions (protein or placebo) and within time points. Independent t tests with Bonferroni corrections will be used to compare time-points between dietary conditions for all measures. Paired t tests will be used to detect any significant within-group changes between time points.

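### The primary outcome (A57) names no marker or time point, and the strength target that sizes the trial (A60) names neither the lift nor the time

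*Protocol*

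**What the plan says.** - **A57 and A58.** The primary outcome is "Exercise-induced changes in markers of muscle damage". The only secondary outcome is "Precision assessment of dual energy X-ray absorptiometry".
- **A6-1 (lay summary).** Damage is assessed "through indirect blood markers (from blood samples), self-perceived muscle soreness (via pressure algometry), and muscle function (strength and flexibility"). On timing it says: "Muscle damage will be assessed before, immediately after, and in 24-hour intervals after the exercise".
- **A13 (both parts).** Blood is analysed for "serum concentrations of creatine kinase, myoglobin (markers of muscle damage), C-reactive protein, and interleukin-6 (markers of inflammation"). A13 adds thigh circumference, range of motion, soreness on a visual analogue scale (VAS) and pressure-pain threshold. These are taken before and immediately after exercise and at +24, +48, +72 and +168 h. For strength, "during visits six and seven, the 1RM strength test will be repeated on the leg press and leg extension"; those visits are +72 h and +168 h. The last strength test before the bout is at visit 2, and the exercise visit follows three weeks later.
- **A60.** Part A is sized on a "between-group difference in muscle strength of 14" per cent, and Part B on 13%. No lift, time or standard deviation is given.
- **A62.** Each marker is analysed separately by ANOVA. Bonferroni correction is attached to the independent t tests between groups at time points. Then: "Paired t tests will be used to detect any significant within-group changes between time points". No correction is mentioned for these.

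**The concern.** A57 asks for the primary outcome measure and receives a class of measures. The reader cannot tell which result decides whether load, sex or milk protein made a difference, or when that result is read. Because A58 moves no marker down, anyone following the plan as written could present whichever marker turned out significant as the primary finding.

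The sample size does not settle the choice. A60 points to strength, but strength is only one candidate under the broad reading of A57 and is not among them under the narrow one. Nor does A60 say whether its targets concern leg press, leg extension or both, or which of the two post-exercise tests they refer to.

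The paired t tests add a smaller risk. A significant change in one group beside a non-significant change in the other is easily read as a group difference, although it does not test one. The objectives in A10 concern comparisons between sexes, loads and diets.

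**Working it through.** **1. The plan's own figures.** A60 states 8 per group (Part A, 14%) and 9 per group (Part B, 13%) for 80% power, two-sided 0.05, dependent t test. With no standard deviation (SD), these can only be solved backwards from non-central-t power:

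- Paired test, n = 8: 80% power needs a standardised effect of 1.156, so the SD of differences is 14 / 1.156 = 12.1 percentage points. Any SD from about 11.0 to 12.1 gives n = 8.
- Paired test, n = 9: effect 1.067, SD 13 / 1.067 = 12.2 (range 11.2–12.2).
- Independent test, n = 8 per group: effect 1.507, SD 14 / 1.507 = 9.3 (range 8.6–9.3).
- Independent test, n = 9 per group: effect 1.407, SD 13 / 1.407 = 9.2 (range 8.6–9.2).

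Nothing in A60 allows these SDs to be matched to a lift or a time. The use of a dependent test for a between-group difference is a separate matter and is not needed here.

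**2. How many markers are primary?**

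- Narrow reading, using the label in A13: creatine kinase and myoglobin = 2. Strength is not included.
- Broad reading, using A6-1 with the measures in A13: 4 blood + 2 soreness (VAS, pressure-pain threshold) + 2 limb (circumference, range of motion) + 2 strength (leg press, leg extension) = 10. A6-1 does not mention circumference; without it the count is 9.

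**3. Family-wise error, one 5% test per marker, no true differences.** For k independent tests it is 1 − 0.95^k:

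| Family | Calculation | Result |
|---|---|---|
| 2 markers | 1 − 0.95² | 9.75% |
| 9 markers | 1 − 0.95⁹ | 37% |
| 10 markers | 1 − 0.95¹⁰ | 40.1% |

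The markers are probably correlated. The documents give no correlations, so a range is assumed. For ten equally correlated normal statistics, simulation gives 35%, 29% and 21% at correlations of 0.3, 0.5 and 0.7.

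One test per marker is generous to the plan: it treats the Bonferroni correction over time points as fully protecting each marker.

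**4. When is strength measured?** A18 counts 8 strength tests over the two parts, so 8 / 2 = 4 per part, matching visits 1, 2, 6 and 7 in A13. It counts 12 for soreness, range of motion and circumference, so 12 / 2 = 6 per part, matching the six times in A13. A13 and A18 therefore agree: two strength tests after exercise, at +72 h and +168 h, and none immediately after, at +24 h or at +48 h. A6-1 includes strength among measures taken immediately after and at 24-hour intervals, and these statements do not agree.

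**5. Side by side.** A57 fixes no marker; A60 sizes on strength; A13 offers two lifts at two post-exercise times. Even if strength is taken as primary, 2 × 2 = 4 lift-by-time combinations remain before any summary of the two lifts is considered.

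**The case against.** Several points on the other side are fair.

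- **The list of ten is inferred.** A57 contains no list, and on the narrow label the family is two. This stands, and is why the error is given as a range. It does not rescue the plan: with two markers, strength is outside the primary outcome and the trial is sized on something else.
- **A statistical analysis plan may exist.** A54 mentions one, and A62 applies Bonferroni to all measures without defining the family. Correction across markers could be set out there, so its absence is not the point. Naming the primary outcome is a protocol matter, and the form asks for it directly.
- **A6-1 is a short lay summary.** True; that discrepancy is minor and a phrase would settle it.

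Three stronger readings may tempt a reader, but the documents do not support them.

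- *The strength target corresponds to nothing the trial measures.* 1RM is measured on both lifts before and after exercise. What is missing is which lift and which time.
- *The trial is underpowered because the effect has faded by +72 h.* The documents give no SD and no time course, and nothing says the 14% was set for another time. In Part A the load comparison also pools the sexes, at about 20 × 0.8 = 16 per load group after dropout rather than 8.
- *The paired tests must yield many chance findings.* A62 does not say that every pair of times is tested, and no change at all after damaging exercise is implausible given A12. A62 also plans between-group tests, so misuse of the paired tests is a risk, not the stated plan.

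**Conclusion.** The concern holds. A57 leaves the primary outcome open over 2 to 10 markers and over time, and A60 sizes both parts on a strength measure that A57 does not single out and that is not tied to a lift or time.

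If every marker is tested at 5%, the family-wise error is about 10% (two markers) to 40% (ten) under independence, and 21–35% for ten at correlations of 0.7–0.3. These figures assume one test per marker and no correction across markers, which is how A62 reads; the correlations are assumptions. The textual findings need no assumption: no marker or time in A57, none moved down in A58, no lift or time in A60, and strength after exercise only at +72 h and +168 h against a visit 2 value from three weeks before the bout. No conclusion is drawn about the power actually available at either time.

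**What to change.** 1. **A57:** name one primary outcome for each part, matching A60. One example is the between-group difference in change in 1RM (one named lift, or the sum of the two) from visit 2 to one of the two scheduled post-exercise times, such as +72 h. The choice belongs to the investigators, but should be made before any data are seen and carried into the trial registration planned in A50.
2. **A58:** list the remaining markers and times as secondary, with a multiplicity correction or as estimates only.
3. **A60:** state which lift and time the 14% and 13% refer to, and confirm that these targets apply at that time.
4. **A62:** report within-group changes as estimates with confidence intervals. Draw conclusions from the between-group comparison, not from the uncorrected paired t tests.
5. **A6-1:** reconcile the description of strength assessment with the schedule in A13.

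As long as the targets can be confirmed for the chosen time, this changes wording only and adds no visit or measurement. If they cannot, the sample size needs a fresh justification. The downside is that the other markers lose primary status.
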